### **7.3 Assessment of adverse events**

#### **7.3.1 Evaluation criteria**

The relation between the adverse event and the study medications must be evaluated according to the data collected. Causality assessment will be made by the investigator for both non serious and serious AEs using the 4-category system defined below.

##### **(1) DEFINITE**

An adverse event that follows a reasonable temporal sequence from the administration of the drug (including the course after the withdrawal of the drug) and that satisfies any of the following:

- Reappearance of similar reaction upon re-administration (re-challenge)
- Positive results in drug sensitivity tests (skin test...)
- Toxic levels of the drug revealed by measurement of drug concentrations in blood or other body fluids.

##### **(2) PROBABLE**

An adverse event that follows a reasonable temporal sequence from the administration of the drug (including the course after the withdrawal of the drug) and for which factors other than the drug, such as underlying diseases, complications, concomitant drugs and concurrent treatments can reasonably be excluded.

##### **(3) POSSIBLE**

An adverse event, that follows a reasonable temporal sequence from the administration of the drug (including the course after the withdrawal of the drug) and for which possible involvement of the drug can be argued (\*), although factors other than the drug, such as underlying diseases, complications, concomitant drugs and concurrent treatments may also be responsible.

(\*) For example, there have been similar reports in the past including reports on its analogues or the occurrence of the event could be predicted from the pharmacological actions / chemical structure of the drug.

#### **(4) UNLIKELY / NOT RELATED**

An adverse event that does not follow a reasonable temporal sequence from the administration of the drug or that can be reasonably explained by other factors such as underlying disease, complications, concomitant drugs and concurrent treatments.

Note: if any essential information for the evaluation including temporal sequence of the adverse event from the administration of the drug (including the course after withdrawal of the drug), underlying diseases, complications, concomitant drugs and concurrent treatments is not available, the case can be cited as "lack of data" at the initial report. However, the adverse event shall be categorised into any of (1)-(4) as soon as possible.

#### **7.3.2 Points to consider**

The following points must also be taken into account during causality assessment of adverse events:

- Timing of the event between administration of the drug and the onset of the adverse event
- Drug levels and evidence, if any, of overdose
- A known or expected response pattern to the suspect drug. This included:
  - Previous experience with the drug and whether the adverse event is known to have occurred with the drug
  - Physiological effect of the drug
  - Is the adverse event known as an adverse event related to other drugs, which belongs to the same or to similar class?
  - Can the event be explained by the pharmacological action or with regard to the findings in animal?
  - Has the patient a specific genetic predisposition (e.g. slow acetylizer)?
- Dechallenge, i.e. when the drug was decreased or stopped, what happened to the adverse event? This includes was the event cured by giving an antidote?
- Rechallenge i.e. when the drug was restarted after the adverse event had disappeared, what happened?
- Alternative explanations for the adverse event, such as the use of other drugs, illness, non-drug therapies, diagnostic tests, procedures or other confounding factors. Did the adverse event also happen with placebo?

## **7.4 Documentation and reporting of serious adverse events**

### **7.4.1 Reporting responsibility**

After signature of the consent form, any serious adverse event occurring, while the patient is in the study or during the 2 weeks after the end of the study, must be reported by the investigator.

### **7.4.2 Reporting procedures**

#### **1- SERIOUS ADVERSE EVENT INITIAL REPORT**

As soon as the investigator has been informed about a serious adverse event, he or she should fill in as precisely as possible the serious adverse event report form and assess the responsibility of the study treatment.

The investigator must fax the form **within one working day** of knowledge of the event to the Safety Contact. This form and the fax machine receipt must be kept in the case report form.

If the event is unexpected and fatal/life-threatening and is considered by the investigator related to the study treatment, the Safety Contact should be informed **immediately** by phone. If necessary, the other investigators participating in the trial will be informed about the occurrence of such a serious adverse event.

The investigator will report any **serious adverse event** to the sponsor of the study (safety contact):

[name], MD, Department of Neurology, University of Ulm/Germany

[contact]

[contact]

Both the investigator and the sponsors safety contact will adhere to the GCP-requirements (§§ 12, 13) on documentation and notification.

**Suspected unexpected serious adverse reactions** (SUSARs) have to be reported to the responsible Ethics Committee at the University of Ulm by the sponsors' safety contact within the defined notification periods according to GCP-V §13 Abs. 2 and 3.

In addition, the sponsors' safety contact will inform the Competent Authorities within the defined notification periods. The other investigators participating in the trial will be informed about the occurrence of such a SUSAR.

In this trial on the fatal disease ALS, the mortality is the efficacy endpoint and the integrity of the trial may be compromised when the blind is systematically broken for reporting of mortality related SUSARs. Therefore each mortality case will be treated as disease-related and will not be subject to systematic unblinding and expedited reporting. The reporting of these events will be completed within one month after last patient's last visit. The independent Data Safety and Monitoring Board (DSMB) will review the safety data every three month in the ongoing trial with recommendation to the sponsor whether to continue, modify or terminate the trial. All cases of SUSARS that are not efficacy endpoints will be reported as usual.

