### **2.3 Known and potential risks and benefits, if any, to human subjects**

The clinical trial programme showed that pioglitazone is well tolerated. With pioglitazone treatment, oedema can occur but is not usually a cause of withdrawal. Weight may increase during treatment, most likely as a result of increases in subcutaneous fat. Despite weight gain the effects of pioglitazone to improve glycaemic control and lipid profile were maintained. There was no evidence of any toxic effect of pioglitazone on the liver. Increases in CPK and LDH can occur transiently during treatment with pioglitazone but are not of clinical significance.

Pioglitazone has been prescribed to over 3.5 million patients worldwide with over 2 million patient years of usage. The majority of use has been in USA. In Europe, it is estimated that more than 200,000 patients have been prescribed the drug on the market.

Liver toxicity similar in severity and outcome to that reported from the market with troglitazone has not been reported with pioglitazone. In some cases of hepatic reactions, including hepatitis, a role for pioglitazone in their aetiology cannot be ruled out but their nature and incidence is similar to those also reported with other oral hypoglycaemic agents including the sulphonylureas and metformin.

Cases of congestive heart failure (CHF) have been reported in temporal association with pioglitazone use. However, since the background rate of this condition is so high in type 2 diabetes (2-3 cases per 100 per year as reported in the literature), it is not possible to ascribe a clear role for pioglitazone in the development of CHF.

Post-marketing surveillance has thus far not detected any life-threatening suspected ADRs with clear causal relationship to pioglitazone not seen in the clinical trials and has therefore confirmed the ADR profile of pioglitazone reported from clinical trials.

Pioglitazone is contraindicated in patients with:

- Known hypersensitivity to pioglitazone or to any of the excipients of the tablet

- Cardiac failure or history of cardiac failure (NYHA stages I to IV)
- Hepatic impairment

Pioglitazone is also contraindicated for use in combination with insulin.

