### 8.2.6 Safety evaluation

The full-analysis set will be used to address issues of safety. Adverse events data will be processed in the statistical analysis after coding according to the MedDRA dictionary.

Adverse events (AEs) will be classified as pre-treatment AEs or treatment-emergent AEs. Analyses will be performed for these classes. Pre-treatment AEs are defined to be AEs, which obviously occurred prior to the first administration of study medication. Treatment-emergent AEs are defined to be AEs, which occurred at or after the first administration of study medication. In case of doubt regarding the timing of AE onset the worst-case scenario will be applied, i.e. the AE will be considered as treatment-emergent.

AEs will be analysed regarding their seriousness, severity, outcome and causality assessment. SAEs will be analysed regarding their severity, outcome and causality assessment. Furthermore, all AEs with possible, probable or definite causal relationship to study medication (causality assessment) will be summarised as 'drug-related' AEs. They will be analysed regarding severity and outcome. All analyses will report frequency counts of subjects by MedDRA SOC and preferred term. Furthermore, treatment-emergent AEs will be presented by preferred term and sorted by frequency.

Listings by subject will be provided for SAEs and for AEs.

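### Section 7.4.2 treats every death as disease-related and waives its expedited reporting, which conflicts with the section's own commitment to GCP-V §13 and leaves the status of investigator causality unclear

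*Protocol*

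**What the plan says.** Section 7.4.2 gives its reason first: "the integrity of the trial may be compromised when the blind is systematically broken for reporting of mortality related SUSARs". It then sets the rule: "Therefore each mortality case will be treated as disease-related and will not be subject to systematic unblinding and expedited reporting". On timing it adds: "The reporting of these events will be completed within one month after last patient's last visit". Only SUSARs that are not efficacy endpoints keep the usual route. Section 3 makes death, with no restriction on cause, the primary endpoint.

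Other provisions bear on the same deaths:

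- **Section 7.4.2, phone rule:** "If the event is unexpected and fatal/life-threatening and is considered by the investigator related to the study treatment, the Safety Contact should be informed" at once by telephone.
- **Section 7.4.2, onward reporting:** the safety contact reports SUSARs to the ethics committee and the competent authorities within set periods, with GCP-V §13(2) and (3) named for the ethics committee. The other investigators are also informed.
- **Section 7.3.1:** "Causality assessment will be made by the investigator for both non serious and serious AEs", on a four-category scale.
- **Section 8.2.6:** "SAEs will be analysed regarding their severity, outcome and causality assessment". Events rated possible, probable or definite are summarised as drug-related.
- **Sections 7.4.3 and 10.2.2:** the monitoring committee is informed of SAEs, has unblinded access and meets every three months.
- **Section 6.10.3:** the safety contact holds a full set of code envelopes, but only an emergency justifies opening one.

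**The concern.** The sentence in 7.4.2 joins two decisions. One defers reporting to protect the blind. The other assigns a cause of death to every patient before any case has been assessed. Only the first can be needed for the stated purpose.

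Suppose a patient dies of acute liver failure, and the investigator rates the event probably related and judges it unexpected. One part of 7.4.2 sends the case onward within the §13(3) limit. Another holds it until the trial is over. The safety contact cannot follow both.

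At stake is whether the ethics committee, the authorities and the other investigators learn of a fatal suspected reaction while patients are still being dosed, and whether the final safety tables can show such a death as drug-related.

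**Working it through.** **1. The deaths the rule covers.** The planning figures in section 8.1 reproduce.

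- Hazard ratio = ln(0.78)/ln(0.60) = 0.486, as stated.
- Schoenfeld events = 4 × (1.960 + 0.842)² / (ln 0.486)² = 60.4, so 61, as stated. Two-stage power with 61 deaths is 80.1%.
- Enrolment = 198/0.9 = 220, as stated.
- If all 220 patients were followed for 18 months: 110 × 0.40 = 44 and 110 × 0.22 = 24.2, about 68 deaths.

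The rule therefore covers all 61 planned deaths, or about 68 under full follow-up. No figure in section 8.1 depends on it.

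**2. Whether any fatal SUSAR keeps the usual route.** The usual route is kept for SUSARs that are not efficacy endpoints. The endpoint is death of any cause, so every fatal SUSAR is an endpoint and none keeps it.

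**3. Whether the regulation in Appendix VIII allows this.** §12(4) lets a protocol exempt events from the investigator's immediate report to the sponsor. §13(2) (15 days) and §13(3) (seven days for fatal or life-threatening cases) contain no such exemption as reproduced. Section 7.4.2 adopts §13(2) and (3) by name, so the conflict is within the protocol.

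**4. The possible delay.** From first enrolment to the last patient's final treatment-period visit is 3 + 18 = 21 months by section 5.6, or 6 + 15 = 21 months by section 8.1. Adding the one month allowed gives up to about 22 months for an early death, against seven days. For a death at the planned interim (11.1 months) the wait is up to 21 − 11.1 + 1 = 10.9 months. These are upper limits, because the text says when reporting is completed and not when it starts. They would be two months longer if the observational follow-up counts towards the last visit.

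**5. Which deaths the waiver affects.** A death rated unlikely/not related is not a suspected reaction, so §13(3) would not require it to be expedited in any case. A related but expected event is also outside §13(3). The waiver of §13(3) reporting therefore changes the handling only of deaths that are both unexpected and suspected to be drug-related. For deaths from ALS progression it adds no protection of the blind.

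**6. Whether causality is overridden.** Sections 7.3.1, 7.4.2 and 8.2.6 require and use the investigator's rating without excepting deaths, and the SAE form in Appendix V has both a death box and a relationship field. Against that stands the instruction to treat each death as disease-related. The text does not say which prevails. If the instruction prevails, no death can enter the drug-related tables; if the rating prevails, nothing is lost there.

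**7. Size of the affected subset.** The protocol gives no rate of fatal drug reactions. If, purely as an assumption, 2 to 5 deaths were such reactions, they would be 2/68 = 3% to 5/68 = 7% of all deaths. An all-cause comparison shows net mortality by arm and cannot attribute single deaths.

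**The case against.** The strongest defence is that this is a reasoned exception to a general rule. Death is the endpoint, routine code-breaking for deaths could harm the trial, and the section states its carve-out openly. The phone rule runs from investigator to safety contact while the waiver concerns unblinding and onward reporting, so both can operate for one death. This is correct about the phone rule. It does not resolve the conflict with §13(3), and by step 5 the exception is wider than its reason needs.

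A reader might infer that a fatal drug reaction cannot be reported during the trial. The protocol does not support this. Each fatal SAE goes to the safety contact within one working day with a causality judgement, and the committee is informed. Appendix VIII also retains §12(6), on further information after a death, and the annual safety report in §13(6).

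A reader might also infer that drug-related deaths are zero by construction. That is one of the two readings in step 6.

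Cardiac failure is a tempting example, because section 2.3 says: "Cases of congestive heart failure (CHF) have been reported in temporal association with pioglitazone use". But the same section lists it as an expected event, and the phone and SUSAR rules need an unexpected one. A fatal case might still qualify, since §3(9) defines unexpected by nature or severity. A fatal hepatic reaction is the clearer example. Section 2.3 lists hepatocellular dysfunction, so that case too rests on severity, but it reports no liver toxicity comparable in severity and outcome to that seen with troglitazone.

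Finally, opening a code for a patient who has died would breach section 6.10.3 as written. This stands, and the fix must cover it.

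**Conclusion.** The point holds as a conflict within section 7.4.2 and an unclear rule for causality. Expedited notice of a fatal, unexpected, suspected drug reaction is withdrawn from the ethics committee, the authorities and the other investigators, for up to about 22 months, although the section adopts a seven-day limit. The status of the investigator's rating for deaths in the section 8.2.6 tables is not fixed.

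The conclusion rests on the text of §13 as reproduced in Appendix VIII and on death of any cause being the endpoint. The 2 to 5 deaths are illustrative and carry no weight in it.

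It would go too far to say that the safety objective is defeated. The committee sees unblinded safety data every three months, and all-cause death is compared by arm at both analyses. Safety reporting is weakened for a small group of deaths whose number is unknown, and the primary analysis is unaffected.

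**What to change.** 1. In 7.4.2, separate the reporting waiver from the causality assessment. State that the cause of death and the investigator's 7.3.1 category are kept for every fatal SAE.
2. Limit the waiver to deaths that the blinded investigator does not rate possibly, probably or definitely related. Unexpected fatal events rated related then follow the existing 7.4.2 and §13(3) route.
3. In 8.2.6, add a table of fatal SAEs by cause of death and causality category, by arm, for the monitoring committee and the final report.
4. Amend 6.10.3 so that the sponsor's safety contact may open a single code for this purpose while site staff stay blind. State how other investigators are notified without disclosing the code.
5. Use one name for the monitoring committee. Section 7.4.2 calls it the DSMB and sections 7.4.3 and 10.2.2 the DMSC, and the safeguard depends on it.

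The cost is a few sentences in two sections, one table, and a few single-patient code breaks in patients whose endpoint has already occurred. Sample size, boundaries and the log-rank analysis do not change.

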## **2- SERIOUS ADVERSE EVENT FOLLOW-UP REPORT**

If new information becomes available after transmission of the initial report, a follow-up report should be completed by using the same form. Follow-up information shall be handled in the same way as the initial information (i.e. within one working day of knowledge). A copy of any hospital reports and results of any lab tests must also be attached.

### **7.4.3 Responsible Nominated Safety Contact**

The fax and telephone numbers of the Responsible Nominated Safety Contact are given in the list provided in the present protocol. Additionally the independent Data Monitoring and Safety Committee (DMSC) will have to be informed if an SAE occurs.

## **7.5 Unblinding of treatment / Emergency identification**

In the case of a medical emergency requiring identification of the treatment taken by the patient, the code may be unblinded. For more information see section 6.10.3 “emergency unblinding procedure”.

## **7.6 Premature discontinuation / Patient replacement**

Each patient can at any time withdraw from the study without personal disadvantages and without stating reasons.

Whenever possible, all patients prematurely discontinuing study medication will continue to be followed and complete all scheduled evaluations for the duration of the study. The reason(s) for premature cessation of a patient's participation during the trial, other than death, should be specified on the case report form. Whenever possible the evaluations scheduled for the end of the treatment period should be performed.

Study treatment may be stopped prematurely if any of the following events occur, according to the judgement of the investigator:

- Significant intolerance of the study medication, or significant clinical or laboratory findings, e.g. increase in ASAT or ALAT >2.5 upper limit of normal
- Significant intercurrent illness or emergency situation requiring cessation of the study
- The patient wishes to terminate his/her participation in the study
- Investigator judgement that it is in the best interest of the patient
- Failure to comply with the investigational procedures
- Pregnancy
- Technical reasons (change of physician, change of address of volunteer/patient)

Patients who have started double-blind treatment will not be replaced.

### 7.6.1 Investigator's responsibility following premature discontinuation of patients

For any patient prematurely discontinuing the study, the investigator must:

- Recover all the treatment units given to the patients
- In as far as possible, carry out all the examinations and tests planned for the final visit after withdrawal of the subject from the study
- Fill in the corresponding pages of the case report form, specifying the date and reason for premature discontinuation
- When applicable, ask the patient the reason of his/her Informed Consent withdrawal while fully respecting the subject's rights
- Where possible prescribe a visit 2 weeks after withdrawal in order to control and document any change in the patient's clinical status. If a serious adverse event occurs, the Responsible Nominated Safety Contact must be informed according to the procedures described in section 7.4 "Documentation and reporting of serious adverse events".

### 7.6.2 Study Termination

Certain circumstances may lead to early termination of an entire study, in particular for ethical or safety reasons such as:

- The high frequency and/or unexpected severity of adverse events,
- Unsatisfactory recruitment of patients in as far as their quantity or quality is concerned or recurrent incomplete/inappropriate collection of data.

The study may be also stopped prematurely if the interim analysis shows pronounced superiority of the intervention group compared to the placebo group (s. section 8.2.5). The decision to prematurely terminate the study will be taken by the sponsor and the investigator.

## 8 STATISTICS

### 8.1 *Sample size and power considerations*

In four previous ALS trials in which the principal investigator was involved, the rate of loss to follow up was less than 1 % (Exonhit/Pentoxifyllin, ONO2506, 5000 mg Vitamin E trial, TCH346-Novartis-Trial). We expect to repeat this low rate, since ALS is a life threatening disease and the centres involved are experienced in the clinical care for the patients.

The study will be conducted using a two-stage group sequential test design within the  $\Delta$ -class of critical values according to Wang and Tsatis. The planned information rates are 0.5 and 1. These information rates fix the weights for combining the p-values using the weighted inverse normal method. The critical values of the group sequential test design were calculated for the standardised (cumulative) test statistic for the design with boundary shape parameter  $\Delta = 0.0$ , i.e. O'Brien/Fleming type design. For one-sided

$\alpha = 0.025$  and the information rates given above the resulting boundary p-values are given by  $p_1 = 0.00258$  and  $p_2 = 0.02400$  with corresponding critical values 2.797 and 1.977, respectively.

For one-sided  $\alpha = 0.025$  and 18-month survival rates of 60% in the standard group and 78% in the test group (hazard ratio = 0.486), the statistical power is 80% if the log-rank test is performed after observation of a total of 31 deaths at the first stage and after 61 deaths (accumulated number) at the second (final) stage (formula of Schoenfeld, ADDPLAN® version 3.1.2, ADDPLAN GmbH, Germany).

Assuming an accrual time of 6 months and a follow-up time of 15 months (21 months observation time) a total of 198 subjects (99 subjects per treatment group, without drop-outs) is expected to yield the necessary number of deaths if the accrual rate is constant (conservative estimation). Under these assumptions, the time points of analyses are expected to be 11.1 months observation time (interim analysis) and 21 months observation time (final analysis).

Thus, considering a drop-out rate of 10%, it is planned to enrol a total of 220 patients.

